### **10.5.2 Skin lesion response rate**

Skin lesion response rate is determined only among patients with at least one skin lesion at baseline, and is the proportion of this group of patients with a response (complete clinical response or partial response) on the Physician's Global Assessment of Clinical Condition (PGA), as described in [Section 7.5.4.1](#). Once a patient begins laser treatment or receives local surgery to treat their skin lesions, any data obtained from that point onward will be excluded from the skin lesion response analysis.

Skin lesion response rate will be compared between the RAD001 and placebo arms in patients from the FAS with at least one skin lesion at baseline, using a one-sided exact Cochran-Mantel-Haenszel (CMH) test with a Type I error rate of 2.5%. The test will be stratified by the protocol stratification factor (TSC and use of EIAED versus TSC and non-use of EIAED versus sporadic LAM). The skin response rate will be presented for each treatment arm, along with exact 95% confidence intervals.

### **10.5.3 Multiplicity adjustment for analysis of main secondary endpoints**

Multiplicity will be controlled via a closed testing procedure. Thus, while the hypothesis tests for the two secondary endpoints described in [Section 10.5.1](#) and [Section 10.5.2](#) will both be carried out, the interpretation of the p-values will depend on the hierarchy used in the closed testing strategy. Based on clinical judgment, it was decided to rank the secondary efficacy endpoints in order of importance: time to angiomylipoma progression, followed by skin lesion response rate. Thus, the closed testing procedure is as follows:

1. Conduct primary analysis to compare RAD001 versus placebo on angiomylipoma response rate using one-sided exact CMH test. If  $p > 0.025$  then STOP - otherwise, declare statistically significant benefit of RAD001 on angiomylipoma response rate, and continue to next step.
2. Compare time to angiomylipoma progression between RAD001 and placebo using a one-sided, stratified logrank test. If  $p > 0.025$  then STOP - otherwise, declare statistically significant benefit of RAD001 on time to angiomylipoma progression, and continue to next step.
3. Compare skin lesion response rate between RAD001 and placebo using one-sided exact CMH test. If  $p > 0.025$  then STOP - otherwise, declare statistically significant benefit of RAD001 on skin lesion response rate.

For example, the first secondary endpoint, namely time to angiomyolipoma progression, can only be formally declared statistically significant if the p-value is less than or equal to 0.025 and the primary endpoint was statistically significant. Similarly, skin lesion response rate can only be formally tested if both the primary endpoint and the time to angiomyolipoma progression were statistically significant. This approach ensures that the overall Type I error rate of the trial is maintained at 2.5% (one-sided).

#### **10.5.4 Additional secondary efficacy analyses**

##### **Duration of angiomyolipoma response**

Duration of angiomyolipoma response is defined as the time from the date of the first angiomyolipoma response until the date of the first angiomyolipoma progression, where angiomyolipoma response and angiomyolipoma progression are as defined in [Section 7.5.2](#). Duration of angiomyolipoma response applies only to patients who achieve an angiomyolipoma response. Duration of angiomyolipoma response will be censored if angiomyolipoma progression is not observed before the first to occur out of (i) the cut-off date for the final analysis, or (ii) the date when a non-study systemic anti-angiomyolipoma therapy is started, or (iii) the date of death. The censoring date will be the date of the most recent CT/MRI assessment before the first of any of these three events occurred.

Duration of angiomyolipoma response will be summarized for patients in the RAD001 treatment arm only. A Kaplan-Meier curve will be constructed, and the median response duration will be presented along with 95% confidence intervals. In addition, the Kaplan-Meier estimates with 95% confidence intervals at 3, 6 and 12 months will be summarized.

##### **Time to angiomyolipoma response**

Time to angiomyolipoma response is defined as the time from the date of randomization until the date of the first angiomyolipoma response, where angiomyolipoma response is as defined in [Section 7.5.2](#). Time to angiomyolipoma response applies only to patients who achieve an angiomyolipoma response, i.e., patients in the analysis will have known times to response and there will be no censored times. Time to angiomyolipoma response will be summarized only in the RAD001 treatment arm. The median time to response will be presented along with a 95% confidence interval, and the proportions of angiomyolipoma responders who respond by 3 and 6 months will be provided.

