### 3.2 Secondary objectives

To compare RAD001 versus placebo with respect to:

1. Time to angiomyolipoma progression.

2. Skin lesion response rate.
3. Change from baseline in plasma angiogenic molecules, e.g., VEGF, basic FGF, PLGF, soluble VEGF receptor1, and soluble VEGF receptor2.
4. Renal function assessed using calculated creatinine clearance
5. Safety as assessed by the National Cancer Institute's (NCI) Common Terminology Criteria for Adverse Events (CTCAE), version 3.0.

In RAD001 treatment arm to:

1. Characterize the pharmacokinetics of RAD001 in this patient population, specifically in terms of exposure.
2. Describe the time to angiomyolipoma response, the duration of angiomyolipoma response, and the duration of skin lesion response.

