Safety evaluations are routinely performed at each visit according to the visit schedule ([Table 7-1](#)). Patient must be in a fasting state (at least 12 hours) at the time of blood sampling for all laboratory evaluations including the lipid profile. Hematology and biochemistry evaluations will be performed according to the visit schedule ([Table 7-1](#)). Note that hematology and biochemistry assessments are performed at screening and do not need to be repeated on Treatment Day 1 if Treatment Day 1 occurs within 14 days of the screening visit. Otherwise, the patient will need to repeat the screening visit blood collections. All blood samples obtained at each visit will be sent to a Central Laboratory for analysis. If laboratory results are requested on an urgent basis, the attending physician will use the local laboratory results for treatment decisions. Complete details regarding all study required safety assessments are provided in [Section 7.6](#).

During this phase of the study, all patients will have a CT/MRI of the kidney performed at 12, 24 and 48 weeks after the start of study treatment, and annually thereafter until angiomyolipoma progression. A CT/MRI of the kidneys should be repeated at the End of Treatment (EOT) visit if the patient has discontinued for any reason other than angiomyolipoma progression, and if it has been more than 8 weeks since their most recent kidney CT/MRI during the first year of treatment, or more than 6 months since their most recent kidney CT/MRI thereafter.

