#### **4.5 Extension phase**

There are two distinct parts of this trial, the core and extension phase. The core phase is from the start of the trial up to the time when the results of the final primary analysis are known. This primary analysis will be performed using all data up to the data cutoff date, which is defined as 6 months after the last patient is randomized. Following a database freeze, the statistical analysis will be performed. During this time, patients will continue on the blinded treatment phase or open-label phase as before, until the time when the results of the final data analysis are known and the core phase of the trial is terminated.

If this final data analysis fails to show superiority of RAD001 over placebo, all patients will be discontinued from the study and will have end of treatment evaluations as indicated in [Table 7-1](#) and [Table 7-2](#). In this case there will be no extension phase.

If the final trial results favor RAD001, then an extension phase will be launched. All patients still receiving study treatment at this time, as well as those being followed for post-treatment evaluation, will be given the option of starting open-label RAD001. Similarly, patients receiving open-label RAD001 at the end of the core phase will be offered to continue into the extension period. The extension phase will run until 4 years after the last patient was randomized, ensuring patient follow-up of 4-5 years (assuming patient accrual over a period of approximately 12 months).

Those patients entering the extension phase, who had previously only been receiving placebo, will have scheduled assessments beginning at Treatment Day 1 according to [Table 7-2](#). Patients that had been on active RAD001 prior to beginning the extension phase will simply continue their sequence of assessments, according to [Table 7-1](#) and [Table 7-2](#). Accordingly, patients that had been on active RAD001 in the Open-label phase prior to beginning the extension phase will simply continue their sequence of assessments according to [Table 7-2](#). Patients in the extension phase will continue to have the same safety and efficacy assessments as in the core phase until angiomyolipoma progression, with the exception of biomarker assessments and pharmacokinetic assessments which will not be performed in the extension phase.

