### 10.4.2 Statistical hypothesis, model, and method of analysis

The primary analysis will be a comparison of the angiomyolipoma response rates in the RAD001 and placebo arms using an exact Cochran-Mantel-Haenszel (CMH) test at the one-sided 2.5% level, analyzed in the Full Analysis Set. The test will be stratified by the protocol stratification factor, which has three categories as follows: (1) TSC as underlying disease and patient using enzyme-inducing anti-epileptic drugs (EIAED) at randomization, (2) TSC as underlying disease and patient not using EIAED at randomization, and (3) sporadic LAM as underlying disease.

The statistical hypotheses are

$$H_0: RR_{RAD} \leq RR_{PLB} \quad \text{versus} \quad H_1: RR_{RAD} > RR_{PLB},$$

where  $RR_{RAD}$  is the probability of angiomyolipoma response on RAD001 and  $RR_{PLB}$  is the probability of angiomyolipoma response on placebo.

Angiomyolipoma response rates will be provided with exact 95% confidence intervals ([Clopper and Pearson 1934](#)). The analysis will be performed using data up to the data cut-off date of the trial, which will be 6 months after the last patient is randomized.

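### Time to angiomyolipoma response is summarised only in observed responders with no censoring, so late responses in late-enrolled patients are truncated and response can look faster than it is

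*Protocol*

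**What the plan says.** Among the secondary objectives for the RAD001 arm, section 3.2 lists: "Describe the time to angiomyolipoma response, the duration of angiomyolipoma response, and the duration of skin lesion response". Section 10.5.4, under its subheading on time to response, fixes how this is done:

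- Analysis set: "Time to angiomyolipoma response applies only to patients who achieve an angiomyolipoma response".
- Censoring: "patients in the analysis will have known times to response and there will be no censored times".
- Summaries: a median with a 95% confidence interval, and "the proportions of angiomyolipoma responders who respond by 3 and 6 months will be provided".

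Four other provisions determine which responses can be observed:

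- Cut-off (section 10.4.2): "which will be 6 months after the last patient is randomized".
- Accrual (section 4.5): "assuming patient accrual over a period of approximately 12 months".
- Scans (section 4.2): "all patients will have a CT/MRI of the kidney performed at 12, 24 and 48 weeks after the start of study treatment", then annually.
- Confirmation (section 7.5.2): a response counts only if a second scan, about 12 and at least 8 weeks later, confirms it.

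Under section 10.4.3, a patient whose response status is unknown counts as a non-responder, and so falls outside the time-to-response summary.

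**The concern.** With staggered entry and a common cut-off, patients differ in how long they can be observed. Every patient has time for a week-12 response to be confirmed, but only early enrollees have time for a week-48 response to be confirmed. A patient who would respond late but reaches the cut-off first is not censored; that patient is simply absent. There are no censored times only because everyone who would supply one has been left out. This is right truncation.

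The denominator of the 3- and 6-month proportions then loses late responders according to enrolment date. The figures would change with a different accrual rate or cut-off even if the drug's effect did not. At stake is the answer to a stated secondary objective: how quickly response occurs on RAD001.

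The same section treats duration of response differently, censoring it at the cut-off and using Kaplan-Meier. Duration naturally conditions on having responded; time to response does not need to.

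**Working it through.** The protocol gives no figure for time to response, so there is none to reproduce.

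**Inputs from the protocol.** Minimum follow-up is 6 months, about 26 weeks (10.4.2). Accrual is about 12 months, about 52 weeks (4.5), so maximum follow-up is about 78 weeks. Scans are at weeks t = 12, 24 and 48 (4.2). The confirmation interval c is 12 weeks, or 8 at the least (7.5.2).

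**Assumptions.** Accrual is uniform, so follow-up is uniform on 26 to 78 weeks. Scans occur on schedule, so week 12 falls within 3 months and week 24 within 6. A response is dated at its first observation. There is no dropout.

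**Step 1: chance that a first response at week t enters the summary.** It must be confirmed by the cut-off, so

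P(t) = min{1, (78 − t − c)/52}.

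| First response | Follow-up needed | c = 12 | c = 8 |
|---|---|---|---|
| Week 12 | 20-24 weeks | 1.00 | 1.00 |
| Week 24 | 32-36 weeks | 42/52 = 0.81 | 46/52 = 0.88 |
| Week 48 | 56-60 weeks | 18/52 = 0.35 | 22/52 = 0.42 |

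The last-enrolled patient, with 26 weeks, can contribute only a week-12 response.

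**Step 2: effect on the reported shares.** If the true shares of first responses at weeks 12/24/48 are a, b and d, the reported shares are proportional to a, b·P(24) and d·P(48). For 45/30/25 with c = 12:

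- Captured: 0.450 + 0.30 × 0.81 + 0.25 × 0.35 = 0.450 + 0.242 + 0.087 = 0.779.
- By 3 months: 0.450/0.779 = 58%, against a true 45%.
- By 6 months: 0.692/0.779 = 89%, against a true 75%.

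The true timing is not in the protocol, so a range is needed (c = 12):

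| True shares, weeks 12/24/48 (%) | By 3 months, true → reported | By 6 months, true → reported | Median week, true → reported |
|---|---|---|---|
| 100/0/0 | 100 → 100 | 100 → 100 | 12 → 12 |
| 80/15/5 | 80 → 85 | 95 → 98 | 12 → 12 |
| 60/25/15 | 60 → 70 | 85 → 94 | 12 → 12 |
| 45/30/25 | 45 → 58 | 75 → 89 | 24 → 12 |
| 40/30/30 | 40 → 54 | 70 → 86 | 24 → 12 |
| 30/35/35 | 30 → 43 | 65 → 83 | 24 → 24 |
| 20/30/50 | 20 → 32 | 50 → 72 | 24 → 24 |

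**Step 3: without the confirmation lag.** Setting c = 0 gives P(24) = 1.00 and P(48) = 30/52 = 0.58. The 6-month share is then 91%, 84% and 76% for 60/25/15, 45/30/25 and 30/35/35, against true values of 85%, 75% and 65%. That is still 6 to 11 points too high.

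**Step 4: does using all patients with censoring help?** In a simulation with 50% eventual responders, 40/30/30 timing and no competing events, a Kaplan-Meier estimate in all RAD001 patients, censored at the last confirmable scan, gave cumulative response of 20.1%, 35.1% and 49.9% at weeks 12, 24 and 48. The truth was 20%, 35% and 50%. This shows that censoring removes the truncation. It does not test how progression or other therapy should be handled.

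**The case against.** The strongest case on the other side has four parts.

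- **The conditioning is open.** Section 10.5.4 says that the summary covers responders and calls the proportions those of responders. It does not present them as probabilities in all treated patients, and the response rate in all randomised patients is reported separately with exact intervals (10.4.2). This stands in part. What goes unsaid is that responder here means response confirmed by a staggered cut-off.
- **The size rests on assumed timing.** This stands. The pilot results in sections 1.4.6 and 1.4.7 give volumes at 12 or 24 months, not times of first response. If responses come early, the bias is small or nil.
- **The median need not move.** A reader might infer that the reported median will be too short. The documents do not support that. Observed times cluster at the scan weeks, so the median moves only when the true week-12 share is below one half and the reported share above it. It shifts for 45/30/25 and 40/30/30 but not for the other profiles in the table.
- **Little depends on it.** A reader might also infer that the efficacy conclusion is compromised. It is not. The summary is single-arm and descriptive, and the closed testing procedure in 10.5.3 covers only response rate, time to progression and skin lesion response.

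None of this removes the mechanism. Under these assumptions truncation cannot make response look slower.

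**Conclusion.** The point holds as a minor to moderate weakness in a descriptive secondary summary. About 12-19% of week-24 and 58-65% of week-48 first responses would be missing from it at the cut-off. The 3- and 6-month shares among responders are biased upward or at best unbiased, and the median may be too short.

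The overstatement is nil if all responses occur at week 12, about 5 points (3 months) and 3 points (6 months) at 80/15/5, and about 13 and 18 points at slower profiles such as 30/35/35. These figures rest on uniform accrual over the planned 12 months, on-schedule scans, a 12-week confirmation interval and the assumed timing. With the cut-off still 6 months after the last randomisation, slower uniform accrual would lengthen the maximum follow-up and lessen the truncation. Later extension-phase data would lessen it too, but not at the core cut-off. The primary result and type I error are unaffected.

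**What to change.** In section 10.5.4:

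1. Report the cumulative incidence of first confirmed angiomyolipoma response in all RAD001 patients at 3, 6 and 12 months, with 95% confidence intervals.
2. Censor patients who could still respond at their last evaluable kidney CT/MRI before the cut-off for which confirmation was still possible. A large reduction still awaiting its confirming scan then does not count as a scan without response.
3. Treat progression, death and start of non-study systemic anti-angiomyolipoma therapy as competing events, using the Aalen-Johansen estimator. Censoring them in 1 minus Kaplan-Meier would overstate cumulative response, because those patients would be treated as still able to respond.
4. Keep the responder-only median and proportions as a descriptive line labelled *among responses confirmed by the cut-off*. They answer a different question, timing given response, and the label states the condition.

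The cost is a reworded paragraph plus one extra table and curve, all from data already collected. The downside is a somewhat less favourable-looking time-to-response figure.

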##### **Duration of skin lesion response**

Duration of skin lesion response is defined as the time from the date of the first skin lesion response until the date of the first skin lesion progression, according to the Physician's Global Assessment (PGA), defined in [Section 7.5.4.1](#). Duration of skin lesion response applies only to patients who achieve a skin lesion response. Duration of response will be censored if skin lesion progression is not observed before (i) the cut-off date for the final analysis, or (ii) the date when a non-study systemic anti-angiomyolipoma therapy is started, or (iii) the date when laser treatment or local surgery to treat skin lesions is started, or (iv) the date of death. The censoring date will be the date of the most recent skin lesion assessment before the first of any of these four events occurred.

Duration of skin lesion response will be summarized for patients in the RAD001 treatment arm only. A Kaplan-Meier curve will be constructed, and the median response duration will be presented along with 95% confidence intervals. In addition, the Kaplan-Meier estimates with 95% confidence intervals at 3, 6 and 12 months will be summarized.

### **10.5.5 Safety**

The assessment of safety will be based mainly on the frequency of adverse events (AEs) and on the number of laboratory values that fall outside of pre-determined ranges. Other safety data (e.g., electrocardiogram, vital signs) will be considered as appropriate. All safety data will be listed.

For all safety analyses, the safety population will be used.

#### **10.5.5.1 Adverse events**

All (AEs) recorded during the study will be summarized. The incidence of adverse events will be summarized by body system, severity (based on CTCAE grades), type of adverse event, and relation to the study treatment. Deaths and SAEs will be listed by patient and type of adverse event.

Adverse events will be summarized by presenting the number and percentage of patients having any adverse event in each body system and having each individual adverse event. Any other information collected (e.g., severity or relatedness to study medication) will be listed as appropriate.

In addition, adverse events of related nature may be analyzed by categories regrouping the relevant preferred terms, as appropriate.

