## Management of amenorrhea

Investigators should be aware of the identified risk of secondary amenorrhea in post-adolescent females. No changes in study drug treatment or treatment with concomitant medications was implemented in prior cases in this study. Nearly all previous cases of amenorrhea for patients on this study resolved spontaneously. Amenorrhea did not result in any treatment discontinuations. If amenorrhea event of 6 months or more is seen, consultations with an endocrinologist, gynecologist, or other appropriate health care personnel are recommended.

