### **7.3.1.4 Endocrine testing**

A blood sample for analysis of total testosterone, FSH and LH (all patients) and estradiol (female patients) will be obtained at the screening/baseline visit and every 12 weeks after the start of study drug. In the event that amenorrhea is reported in between scheduled assessments, hormone evaluations should be completed at that time.

For patients who have already been randomized and did not have the endocrine parameters tested, there will be no retrospective analysis of blood samples.

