#### **7.6.5.7 Reproductive history and endocrine testing**

In order to provide additional follow-up on cases of amenorrhea, increased hormonal evaluation will be performed and supplemental medical history will be collected.

Additional menstrual history (age at menarche, previous cases of amenorrhea or menstrual disorders, biological mother’s age at menopause) and pregnancy history (pregnancies, full-term gestations, abortions, live births, miscarriages) will be collected one time after implementation of protocol amendment 3. Following implementation of amendment 3, menstrual status will be collected monthly via patient diary. Every 12 weeks, data from patient diary will be collected at clinical site for CRF. It is recommended that study coordinators contact patients monthly for the first 3 months to remind patients to document menstrual status in patient diary.

A blood sample for analysis of total testosterone, FSH and LH (all patients) and estradiol (female patients) will be obtained at the screening/baseline visit and every 12 weeks after the start of study drug. In the event that amenorrhea is reported in between scheduled assessments, hormone evaluations should be completed at that time.

For patients who did not have the endocrine parameters tested, there will be no retrospective analysis of blood samples.

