### **10.1 Populations for analysis**

The **Full Analysis Set (FAS)** consists of all randomized patients. Following the intent-to-treat principle, patients are analyzed according to the treatment and stratum that they were assigned to at randomization. The FAS will be the primary population in the assessment of efficacy.

The **Per Protocol Set (PPS)** will consist of all patients from the FAS without any major protocol deviation, who are evaluable for efficacy and who have completed a minimum exposure requirement. However, if a patient progressed, discontinued for adverse event or died before the minimum exposure requirement could be met, or before he/she was evaluated for efficacy, that patient will still be included in the PPS. Patients will be evaluable for efficacy if they have a known angiomyolipoma response status. The minimum exposure requirement is defined as having a relative dose intensity over the first 12 weeks of treatment of at least 50%. The PPS will be used for a supportive analysis of the primary endpoint.

The **Safety Population** will consist of all patients who received at least one dose of study treatment and had at least one post-baseline safety assessment (where the statement that a patient had no adverse event (on the Adverse Events CRF) constitutes a safety assessment). Patients will be analyzed according to treatment received.

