### **10.2 Patient demographics/other baseline characteristics**

Demographic and other baseline characteristics will be listed and summarized by treatment group using the FAS.

Qualitative data (e.g., gender, race, WHO performance status) will be summarized by means of contingency tables for each treatment group, and quantitative data (e.g., age, body weight) will be summarized by appropriate descriptive statistics (mean, standard deviation, median, minimum and maximum) for each treatment group.

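### Amenorrhea will be shown as a percentage of all treated patients, men included, which understates the risk in women by the share of men

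*Protocol*

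**What the plan says.** Three statements together set the rule.

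- Section 10.5.5: "For all safety analyses, the safety population will be used".
- Section 10.1 defines that population as "all patients who received at least one dose of study treatment and had at least one post-baseline safety assessment". Sex plays no part in the definition, and section 5.1 admits men and women.
- Section 10.5.5.1 has adverse events summarized as the "number and percentage of patients having any adverse event in each body system and having each individual adverse event".

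The protocol gives amenorrhea special attention elsewhere. Under the management of amenorrhea in section 6.1.1: "Investigators should be aware of the identified risk of secondary amenorrhea in post-adolescent females". Section 7.3.1.4 adds unscheduled testing: "In the event that amenorrhea is reported in between scheduled assessments, hormone evaluations should be completed at that time". Section 7.6.5.7 gives the reason for the extra collection: "In order to provide additional follow-up on cases of amenorrhea, increased hormonal evaluation will be performed and supplemental medical history will be collected". No section attaches a denominator to this event.

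Where only some patients can have an outcome, the protocol does restrict a denominator. Section 10.5.2: "Skin lesion response rate is determined only among patients with at least one skin lesion at baseline".

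**The concern.** Men cannot have amenorrhea. They add nothing to the numerator, but under the general rule they are counted in the denominator. A column headed percentage of patients is not false, but it is a poor measure of a risk borne only by women, and this is a risk the protocol has singled out for follow-up. A reader who takes the tabulated figure as a woman's risk on RAD001 gets too low a number.

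The shortfall is not fully repaired elsewhere. Counts and listings let a reader rebuild the rate in women, but the planned table of sex follows section 10.2: "Demographic and other baseline characteristics will be listed and summarized by treatment group using the FAS". It is therefore by randomized group. Under sections 4.3 and 4.5 placebo patients may start open-label RAD001. From then on, that table does not directly give the number of women exposed to the drug.

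**Working it through.** The protocol states no amenorrhea rate and no sex mix, so there is no planned figure to reproduce. The check is an identity followed by a range.

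**Identity.** Within an arm, men contribute no cases, so

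cases / all patients = (cases / women) × (women / all patients).

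Write *s* for the share of women. The displayed percentage is the incidence in women × *s*. The relative understatement is 1 − *s*, and the factor needed to recover the rate in women is 1/*s*. This needs no assumption.

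**Inputs for a range.**

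- Sporadic LAM share: 25% (section 10.7 expects about 75% TSC) or 10% (the alternative scenario in section 10.7).
- All sporadic LAM patients are women: assumed. Section 1.1 gives the prevalence per million women but does not state this.
- 50-60% of TSC patients are women: assumed, with no source in the protocol.
- Planned RAD001 arm: 66 patients (section 10.7).

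**Share of women**, *s* = (1 − LAM) × f + LAM, where f is the share of women among TSC patients:

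| LAM | f | s | 1 − s | 1/s |
|---|---|---|---|---|
| 0.25 | 0.5 | 0.75 × 0.5 + 0.25 = 0.625 | 37.5% | 1.60 |
| 0.25 | 0.6 | 0.75 × 0.6 + 0.25 = 0.70 | 30% | 1.43 |
| 0.10 | 0.5 | 0.90 × 0.5 + 0.10 = 0.55 | 45% | 1.82 |
| 0.10 | 0.6 | 0.90 × 0.6 + 0.10 = 0.64 | 36% | 1.56 |

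Women among the 66 on RAD001: 66 × 0.55 = 36.3 to 66 × 0.70 = 46.2, so about 36 to 46.

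**Illustration with an assumed count.** Ten cases among 66 patients display as 10/66 = 15.2%. In women the rate is 10/46 = 21.7% to 10/36 = 27.8%.

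**Wider assumption.** If the share of women could be anywhere from 50% to 90%, the understatement runs from 50% down to 10%. An incidence of 15% in women would display as 7.5% at *s* = 0.5 and 13.5% at *s* = 0.9.

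**Comparison between arms.** With the same share of women in both arms, *s* cancels and the ratio is unchanged. A chance imbalance would shift it. Take assumed rates in women of 15% and 5%, a ratio of 3.0:

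- 60% women on RAD001 and 75% on placebo: 15 × 0.60 = 9.0% against 5 × 0.75 = 3.75%, a ratio of 2.4.
- The shares reversed: 15 × 0.75 = 11.25% against 5 × 0.60 = 3.0%, a ratio of 3.75.

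**The case against.** The best reply is that this is detail for the SAP or the table shells, and the SAP is not at hand. Section 10.5.5.1 does not spell out a denominator. Naming the safety population does not forbid using a subset of it, so a female denominator could be set later without contradicting the protocol. The skin lesion comparison is also imperfect: that is a formally tested endpoint whose denominator has to be fixed, whereas adverse event tables are descriptive. Menstrual diaries, hormone results and listings give other routes to the same information. The sex mix used above is assumed. All women is itself not the true at-risk group, because postmenopausal and oophorectomized women are in it.

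Much of this stands. The all-patient denominator is the natural reading, not an explicit statement. No inference depends on it, and the size cannot be fixed from the protocol. What does not stand is the claim that the protocol is merely silent. It sets one rule for every event and one population for all safety analyses, and following them as written gives the diluted figure. The point about women not at risk means that a women-only denominator still errs on the low side. It is nevertheless closer to the risk than one that includes men.

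**Conclusion.** The concern holds, as a minor one. Under the natural reading of sections 10.1, 10.5.5 and 10.5.5.1, the tabulated percentage for amenorrhea is too low as a measure of risk in women by exactly the share of men in the arm. That part is arithmetic.

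The size, a 30-45% understatement or a rate in women 1.43-1.82 times the displayed one, rests on two assumptions: that all sporadic LAM patients are women, and that 50-60% of TSC patients are. Case counts and the expected ratio between arms are unaffected. So are the primary endpoint, the power, the error rate and every decision rule.

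**What to change.** Add to section 10.5.5.1:

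> Amenorrhea and other menstrual adverse events will be reported with female patients in the safety population as the denominator, by treatment.

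A further rate among women menstruating at baseline could be given as an option. It should not be the main figure, because the menstrual history and diaries began only with amendment 3 and are incomplete.

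The cost is one sentence and one changed denominator in the adverse event tables. Section 7.3 already collects sex for every patient, so no new data are needed.
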